## Abstract

**Abstract:**

**Introduction:**

This study aims to enhance aftercare for individuals with acquired brain injury (ABI), focusing on an active lifestyle and health-related quality of life, by implementing a multidisciplinary intervention using a network of outpatient rehabilitation and community-based services, and by evaluating its implementation process and outcomes.

**Methods and analysis:**

The ABI-MOTION intervention includes 5 activities delivered through a network of outpatient rehabilitation and community-based services: outpatient rehabilitation, education flyer, introduction to a sports consultant, maximum of 8 hours of sports consultancy and follow-up by a rehabilitation physician. This hybrid type 2 implementation study focuses on implementation outcomes and uses the RE-AIM (Reach, Effectiveness, Adoption, Implementation and Maintenance) framework for a process evaluation (primary) and effect evaluation (secondary). Sixty individuals with ABI will be followed over time, allowing interim evaluation and optimisation of ABI-MOTION. The first group (control) receives outpatient rehabilitation and follow-up, the intervention group receives all 5 activities of the ABI-MOTION intervention. Data related to the implementation will be collected using field notes, focus groups and semi-structured interviews. To explore the effects of the ABI-MOTION intervention, functional and cognitive tests, self-report questionnaires and home measurements will be conducted just before the intervention and at 3, 6 and 12 months post-discharge.

**Ethics and dissemination:**

The study protocol is approved by the Medical Ethics Committee of Erasmus MC (MEC-2023-0623). The results of the study will be disseminated in peer-reviewed journals, conferences and stakeholder meetings.

**Trial registration number:**

NCT06058351.

STRENGTHS AND LIMITATIONS OF THIS STUDYThe iterative design allows the research team to adjust the acquired brain injury (ABI)-MOTION intervention continuously based on ongoing findings.The collection of both quantitative and qualitative data from individuals with ABI and stakeholders from the network provides a comprehensive understanding of the feasibility of the ABI-MOTION intervention in care and aftercare practice.The combination of existing care and aftercare increases the likelihood of successful and sustainable implementation of the ABI-MOTION intervention.The involvement of researchers in participant recruitment limits the ability to fully observe the course of the implementation process during the recruitment phase of the ABI-MOTION intervention.

## Background

 Acquired brain injury (ABI) refers to any brain damage that occurs after birth.^1^ Stroke and traumatic brain injuries (TBIs) are the most common causes of ABI, with annual global incidence rates of approximately 12 million^2^ for stroke and 69 million^3^ for TBIs. Many people experience long-term consequences of ABI in physical, psychosocial and cognitive functioning.^4 5^ These impairments have a detrimental impact on health-related quality of life (HR-QoL) and participation in society, and may pose challenges for integrating and sustaining a physically active lifestyle after the injury.^6^,^10^

Indeed, individuals with ABI are found to be less physically active than healthy individuals and to have difficulties returning to pre-injury physical activity (PA) levels.^11^,^15^ Also, they often do not adhere to the physical behaviour (PB) recommendations for people with a disability.^11^,^15^ PB can be considered in a 24-hour cycle of PA, sedentary behaviour (SB) and sleep,^16^ with exercise being a specific type of PA, usually performed to improve physical fitness.^17 18^ In the current study, the focus is on integrating and maintaining an active lifestyle by promoting sports and exercise, encouraging everyday PA, such as gardening or walking, and reducing SB. This is particularly important for people with a disability, as it can help alleviate fatigue, anxiety and depression, improve physical fitness, cardiovascular fitness and HR-QoL, and reduce the risk of chronic comorbidities.^19^,^22^

In the Netherlands, community-based services provide guidance to help individuals with ABI adopt an active lifestyle, including consultation to identify suitable sport or exercise opportunities, which has been shown to be effective.^23 24^ However, the connection of these services with clinical rehabilitation or aftercare is not standard practice, creating difficulties for individuals with ABI to locate and access them. Therefore, the overall aim of this study is to improve aftercare for individuals with ABI by promoting an active lifestyle and enhancing HR-QoL. To this end, an intervention (ABI-MOTION) will be implemented using a network of outpatient rehabilitation and community-based services, and its implementation and effects will be evaluated.

## Methods and analysis

### Study design

ABI-MOTION is a hybrid type 2 implementation study,^25^ with implementation outcomes as the primary focus. The study includes a process and effect evaluation, using the RE-AIM framework (Reach, Effectiveness, Adoption, Implementation and Maintenance).^26^ The study protocol has been registered on ClinicalTrials.gov (NCT06058351) and approved by the Medical Ethics Committee of Erasmus MC (MEC-2023-0623). A logic diagram of the ABI-MOTION study is presented in figure 1. The logic diagram provides a schematic overview of inputs, aims, and activities of the ABI-MOTION intervention, the implementation process evaluation (primary) and effect evaluation (secondary) parts, and the outcomes and outputs of the study. The start date of the study was 1 March 2024 and the planned end date of the study is 1 March 2027.

**Figure 1 F1:**
[figure not shown]
Logic diagram of ABI-MOTION. ABI, acquired brain injury; RE-AIM, Reach, Effectiveness, Adoption, Implementation and Maintenance.

### Patient and public involvement

To identify the stakeholders relevant for patient and public involvement in the ABI-MOTION project, we initially engaged the most apparent stakeholders, including individuals with ABI, physical therapists, movement therapists and a community-based service involved in sports and exercise consultancy. Through discussions with these stakeholders, we explored whether any stakeholders were missing. This revealed other relevant stakeholders, such as physicians from the rehabilitation centre, other community-based services involved in sports provision and the association of individuals with brain injuries in the greater Rotterdam region.

The stakeholder group consisted of two individuals with ABI and one partner of an individual with ABI. In addition, we involved a physical therapist, a rehabilitation physician and a movement therapist from the rehabilitation centre. Furthermore, a representative from the association of individuals with brain injuries in the greater Rotterdam region was included, as well as a representative from the community-based service.

Individuals with ABI were involved during the grant application phase, by providing input on the relevance and feasibility of the study. They also contributed to the development of the study protocol, to ensure that the research questions, outcome measures and time investment were in line with their needs, experiences and abilities. During the study, individuals with ABI (ie, study participants) will continue to be involved in optimising the ABI-MOTION intervention through focus groups and semi-structured interviews. At least 4 focus groups and 8 semi-structured interviews will be organised throughout different phases of the study.

To optimise the implementation and study outcomes, an independent user committee has been established. The user committee also includes individuals with ABI, representatives from other rehabilitation centres and professionals from community services in different regions. The role of the committee is to provide independent feedback on the study design, process and outcomes. In addition, the researchers may ask specific questions to the committee for advice. The committee will meet once a year. The insights and recommendations from the user committee sessions will be used for dissemination plans and for drafting a plan for scaling the ABI-MOTION intervention to other regions.

The major changes made as a result of the patient and public involvement to the grant application and subsequent study protocol included the inclusion of a control group prior to the implementation of the ABI-MOTION intervention and the delivery of the sports consultation on an individual basis instead of in a group format. Throughout the study, the ABI-MOTION intervention protocol may be further adapted based on feedback obtained from the focus groups, semi-structured interviews and meetings of the user committee.

### Network

Rijndam Rehabilitation and MEE Rotterdam Rijnmond are the two main network partners. Rijndam Rehabilitation is an inpatient and outpatient rehabilitation provider with 15 locations in the Rotterdam region, which is an urban region in the mid-western part of the Netherlands.^27^ MEE NL is a cooperative association of 20 regional MEE organisations aiming to improve social participation for everyone, including people with a disability.^23^ The sports consultancy programme (SportMEE) is a community-based initiative, funded by the municipality of Rotterdam that aims to advise and guide individuals with disabilities to exercise, sport and an active lifestyle. This sports consultancy is tailored to the patient and may entail guidance to an active lifestyle, support in finding a suitable sport or exercise location, practising with travelling to a sport or exercise location and easily accessible support in the long-term.^24^

Other stakeholders in the network include community-based sports and exercise initiatives in the Rotterdam region, such as those supporting healthcare professionals in finding sports activities for their patients and those engaged in creating new sports provision.

### Study population

The study population will consist of individuals with ABI, healthcare professionals from Rijndam Rehabilitation, including physical and movement therapists and rehabilitation physicians, sports consultants from the community-based service and other stakeholders from the network. Inclusion criteria for individuals with ABI are that they are receiving outpatient rehabilitation at Rijndam Rehabilitation and are at least 18 years of age. Individuals with a life expectancy of less than 1 year or with severe cognitive impairments that preclude providing informed consent and sufficient understanding of study procedures are excluded from the study. Capacity to consent and participate is assessed by the treating rehabilitation physician.

### Power analysis

Since the implementation process is the primary outcome, this study is powered based on the number of individuals with ABI who will receive sports consultancy through the SportMEE programme. Currently, less than 10% of the target population receives sports consultancy via SportMEE. After implementation of the ABI-MOTION intervention, we hypothesise that the reach of the programme will increase to 60%. This means that 60% of participants introduced to the sports consultant during rehabilitation will continue with the optional SportMEE consultancy programme after rehabilitation discharge. Based on these proportions and using an intervention group and a control group with a 3:1 allocation ratio, a two-sided alpha of 0.05 and a power of 0.80, a total sample size of 48 participants is required, 36 in the intervention group and 12 in the control group, as calculated with the Fisher’s exact test. Based on this calculation and taking into account a potential drop-out of 20%, we strive to include a cohort of 60 patients, starting with 15 participants before implementation of the ABI-MOTION intervention, followed by 45 participants in the intervention group after implementation.

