### ABI-MOTION intervention

The ABI-MOTION intervention consists of 5 activities (figure 1). The programme starts with outpatient rehabilitation for patients with ABI (1), provided in the rehabilitation centre by a multidisciplinary team which may include a rehabilitation physician, physical therapist, occupational therapist, psychologist and/or movement therapist. In addition, during outpatient rehabilitation a brain education flyer is provided by a physical therapist (2), with information about ABI, PB guidelines and benefits of an active lifestyle. The community-based service will be integrated in outpatient rehabilitation by arranging an introduction of the participant to a sports consultant during outpatient rehabilitation (3). After rehabilitation discharge, patients may receive a maximum of 8 hours of sports consultancy, depending on their needs, which is delivered by the sports consultants of the SportMEE programme (4). There are no eligibility criteria for the SportMEE consultancy programme. About 6 and 12 months after rehabilitation discharge, the patient has follow-up consultations with the rehabilitation physician (5) as part of outpatient rehabilitation care. The control group receives activities 1 and 5. The intervention group receives all 5 activities.

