### Evaluation of implementation process

The evaluation of the implementation process addresses the RE-AIM dimensions: reach, adoption, implementation and maintenance (table 3). These dimensions will be explored through both quantitative and qualitative methods, including documentation, registration, focus groups, semi-structured interviews and network meetings.

Reach will be assessed by quantifying the extent to which the intervention successfully reached the target population (ie, individuals with ABI who follow outpatient rehabilitation). This will be expressed in the total number of patients in outpatient rehabilitation, the number of potential participants identified and those invited, included and excluded from the study. In addition, reasons for non-inclusion will be systematically documented to gain insight into recruitment barriers and representativeness of the study population.

Regarding adoption, the focus will be on the contextual factors that influence the uptake of the intervention, as well as the perceived acceptability and feasibility among all stakeholders. In assessing these aspects, the focus will be on whether the ABI-MOTION aligns with existing care processes, adoption of ABI-MOTION at the organisational level and stakeholder experiences throughout the process of optimising the ABI-MOTION intervention.

The implementation dimension will be expressed in the extent to which the ABI-MOTION protocol was adhered to in practice. This includes measures of dose delivered and dose received, for example, number of introductions to sports consultant during outpatient rehabilitation. These kinds of protocol adherence and deviation measures will be documented and described.

Finally, maintenance will be evaluated using the Care Process Self-Evaluation Tool (CPSET)^31^ filled in by healthcare professionals. In addition, barriers and facilitators for sustained delivery of the ABI-MOTION intervention after the inclusion period and research phase will be explored.

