### Statistical and qualitative analyses

Descriptive statistics will be used to summarise the documented numbers related to the evaluation of the implementation process and the outcomes of the effect evaluation. Means and SD will be calculated for variables on an interval scale, and medians and IQRs for ordinal variables and if variables are not normally distributed. Proportions will be calculated for nominal variables. ATLAS.ti software (V.24, ATLAS.ti Scientific Software Development GmbH, Berlin, Germany) will be used to analyse and interpret the qualitative data of the focus groups and network meetings. The dimensions and subthemes of the RE-AIM framework, and the BCW, will be used to thematically identify and describe the themes that are discussed.

The changes over time (T0–T3) of the effect outcomes will be analysed with Generalised Estimating Equations (GEE) models for repeated measurements on an intention-to-treat basis using SPSS (V.32, IBM SPSS Statistics, New York, USA). This method takes all observations into account, even if some outcomes are missing, assuming that these data are missing at random. Each parameter at each time point will be included as the dependent variable in separate GEE models. Independent variables that will be added to each model include measurement time (T0, T1, T2 and T3), group (intervention vs control), and the interaction between time and group. In post-hoc analyses, differences between the intervention and control group at each time point will be analysed. If differences in participant or clinical characteristics between the control and intervention group are present, the models will be adjusted for patient characteristics (eg, age, sex and living status) or clinical characteristics (eg, type of injury, type of treatment and comorbidity). Maximal number of covariates in the model will be based on the number of participants in both groups. Potential differences in participant and clinical characteristics between the control group and intervention group will be calculated using independent t-tests for normally distributed interval scale variables, the Mann-Whitney U test for non-normally distributed interval scale variables, and the χ^2^ test for categorical variables. Interim analyses will be performed when all patients from the control group or intervention group have finished the baseline, 3 and/or 6 months follow-up visits.

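### The SportMEE uptake comparison that sizes the study sets rates with different denominators against each other and does not reappear among the stated reach outcomes or analyses

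*Protocol article*

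**What the plan says.** The Power analysis section makes SportMEE uptake the basis of the sample size: "this study is powered based on the number of individuals with ABI who will receive sports consultancy through the SportMEE programme". The starting rate is given as "Currently, less than 10% of the target population receives sports consultancy via SportMEE". The section on the implementation process identifies the target population as people with ABI in outpatient rehabilitation. The rate hoped for is 60%, described as the programme's reach and then explained: "This means that 60% of participants introduced to the sports consultant during rehabilitation will continue with the optional SportMEE consultancy programme after rehabilitation discharge". With 3:1 allocation, two-sided alpha 0.05, power 0.80 and Fisher's exact test, this gives 36 + 12 = 48, raised to 45 + 15 = 60 for 20% drop-out.

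On what each group gets, the ABI-MOTION intervention section says: "The control group receives activities 1 and 5". The introduction to the consultant is activity 3 and the consultancy is activity 4. The intervention group is to receive all five.

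Reach is defined again under Evaluation of implementation process, and in the same terms in Table 3. There it consists of the number of patients in outpatient rehabilitation, "the number of potential participants identified and those invited, included and excluded from the study", and reasons for non-inclusion. SportMEE uptake is not in the list.

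The Statistical and qualitative analyses section says: "Descriptive statistics will be used to summarise the documented numbers related to the evaluation of the implementation process". GEE models are assigned to the effect outcomes. The t, Mann-Whitney and chi-square tests are assigned to differences in participant and clinical characteristics. Fisher's test is not mentioned there.

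**The concern.** Three statements that should describe one quantity do not line up.

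- **Denominator.** One rate is a share of all outpatients with ABI, the other a share of those already introduced to a consultant. Controls are not introduced, so the second rate cannot be formed for them.
- **Outcome.** The word reach means SportMEE uptake where the study is sized and recruitment into the research where outcomes are defined.
- **Analysis.** A two-sided between-group test is powered, but the analysis stated for process numbers is descriptive.

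At stake is the only hypothesis that justifies 60 participants. Left as it is, the uptake definition, the denominator, the time window and the way uptake is established in controls can all be settled after the data are seen. If uptake is then calculated among introduced participants only, anyone whose introduction did not take place leaves the denominator. In an implementation study those are failures that a reach figure ought to include.

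**Working it through.** **Step 1: reproduce the plan's figures.** Inputs from the Power analysis section: control rate p1 = 0.10 (the upper end of what is stated), intervention rate p2 = 0.60, ratio r = 3, two-sided alpha 0.05, power 0.80. Pooled rate p = (0.10 + 3 × 0.60)/4 = 0.475; difference d = 0.50.

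Uncorrected control-group size:

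n = [1.960 × √(4 × 0.475 × 0.525) + 0.842 × √(3 × 0.10 × 0.90 + 0.60 × 0.40)]² / (3 × 0.50²) = 8.73, so 9 (9 + 27 = 36).

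With the Fleiss continuity correction, which approximates Fisher's test:

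n' = (8.73/4) × [1 + √(1 + 2 × 4/(8.73 × 3 × 0.50))]² = 11.24, so 12 (12 + 36 = 48).

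Drop-out: 48/0.80 = 60, 12/0.80 = 15, 36/0.80 = 45. All stated figures reproduce. Enumerating both binomial distributions exactly, Fisher power at 36 versus 12 is 0.90, so the design has some slack at its own assumptions.

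**Step 2: put the intervention rate on the whole group.** Let f be the share of intervention participants actually introduced, and assume that nobody takes up SportMEE without an introduction. Then group-level reach = 0.60 × f. The documents give no value for f; the range below is an assumption. Exact two-sided Fisher power, control rate 10%:

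| Introduced (f) | Group-level reach | 36 vs 12 (after drop-out) | 45 vs 15 (all enrolled) |
|---|---|---|---|
| 100% | 60% | 0.90 | 0.96 |
| 90% | 54% | 0.81 | 0.90 |
| 80% | 48% | 0.68 | 0.79 |
| 70% | 42% | 0.52 | 0.65 |

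The last column applies if uptake is established for everyone enrolled, including those who drop out of the measurements. The plan says less than 10%; at an assumed control rate of 5%, the 45 versus 15 column becomes 0.99, 0.98, 0.93 and 0.85.

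**Step 3: size of the overstatement.** At f = 80%, 36 of 45 are introduced and 0.60 × 36 = 21.6 would be expected to continue. Among those introduced this is 60%; over the group it is 21.6/45 = 48%, a gap of 12 percentage points. At f = 100% the gap is zero.

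**Step 4: precision.** At the hoped-for 27 of 45 (60%), the exact 95% confidence interval is 44% to 74%. A bare percentage would hide that width.

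**Step 5: look for the powered comparison elsewhere.** Reach (Table 3 and text) holds recruitment counts. Implementation (Table 3) covers adherence for the new activities; the text adds dose delivered and dose received, with introductions as the example. Controls are not given the new activities. Neither place names SportMEE uptake in controls, and the analysis section names no between-group analysis for it.

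**The case against.** The strongest reply is that the intervention group is meant to receive all five activities. By design, those introduced are then the whole intervention group and the 60% is a group rate. The absence of an introduction in controls is the contrast under study, and the number who receive consultancy can be counted in both groups. This largely stands: within the intervention group the denominators part only if introductions fail. Yet the plan itself records introductions as a measure of adherence, so it does not take full delivery for granted. Even at full delivery, the 10% describes all outpatients and the 60% describes people who consented to the study.

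Second, failed introductions are counted under the Implementation dimension, and intervention-group uptake may well be captured as dose received. That is fair. It answers any charge that such failures go unrecorded, but it supplies no uptake figure for controls.

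Third, this is a journal article and the test may be set out in a fuller document. Fisher's test is named in the Power analysis section, so a reader might infer that it will be done. Silence alone would be no finding. The difficulty is that the analysis section does speak about process numbers, and what it assigns them is descriptive.

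A reader might go further and infer that the primary hypothesis cannot be answered, or that the sample size is wrong. The documents support neither: the data could be collected and the test run, and the arithmetic is sound.

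**Conclusion.** The point holds as a mismatch within the protocol article that should be fixed. The comparison that justifies 60 participants uses rates with different denominators and does not appear among the stated reach outcomes or analyses.

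Upward bias in reach is conditional: it arises only if some introductions fail and uptake is then reported among introduced participants. The power loss is conditional too. It rests on an assumed share introduced and a control rate of 10%, and it is much smaller when everyone enrolled is counted: about 80% introduced still gives roughly the planned power at 45 versus 15. No change to the number of participants follows from this.

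**What to change.** 1. Name SportMEE uptake after discharge as the reach outcome, with all enrolled participants in each group as the denominator. Establish it in the same way, and over the same stated follow-up window, in both groups.
2. Add to the analysis section the two-sided Fisher's exact test, the risk difference with 95% confidence interval, and intervention-group reach with an exact 95% confidence interval.
3. Report uptake among introduced participants as a secondary figure.
4. Label the Table 3 counts as study recruitment.

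The alternative is to call the uptake comparison descriptive and withdraw the power claim.

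The cost is wording, plus a check of SportMEE use in the 15 controls, either from records or by asking participants. SportMEE is run by a separate organisation and the article does not say whether consent covers its records, so that should be settled before choosing the source. The headline reach figure may be less favourable than one restricted to introduced participants. No extra participants are needed.
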